### Statistical considerations

For primary and secondary outcomes, we will adhere to the intention-to-treat (ITT) principle and analyze all randomized participants, irrespective of attrition. The primary hypothesis will be tested on a superiority framework. Variables from ambulatory BP will be treated as diurnal, nocturnal and 24-h for both systolic and diastolic BP. Mixed effects models will be used to determine differences between groups using final values for systolic and diastolic ambulatory BP, adjusted for baseline values (pre-intervention). If these data present low linear fit, we will compare groups using generalized estimating equations with an independence model as the covariance matrix.

Two analysis sets will be established as follows: (1) a full analysis set (FAS) including all randomized subjects, therefore allowing ITT analyses; and (2) a per-protocol (PP) analysis set including all subjects that completed the trial (completers) with adherence to at least 70% of the intervention sessions (≥ 25 sessions for participants allocated in the exercise program, and ≥ eight sessions for participants allocated to the education program). Participants that drop out of the study due to safety concerns or other outcomes will not be censored in PP analysis. Additionally, we plan to carry out a subgroup analysis stratifying both groups by individuals with non-controlled BP before the intervention versus individuals with well-controlled BP before the intervention. Such stratification will be based on tertiles of systolic BP at baseline, with a primary interest in the comparison of interventions on ambulatory BP using the lowest and highest thirds.

Incomplete data will be explored in sensitivity analyses by pattern mixture model. This procedure will describe whether there is an interaction between the main missing patterns and other variables (e.g., group, time, group by time, BP status, BP status by group). We expect two main missing data patterns based on an indicator of completers versus non-completers (defined as randomized subjects without 12-week data). Because withdrawals may occur due to specific harms or other non-anticipated reasons, we will assess whether additional grouping (indicator) should be made due to different patterns of missing data. Therefore, we will qualitatively document reasons and details of withdrawals on a case-by-case basis. In the case of identifiable patterns indicating that missing data are nonignorable, the interpretation of related findings should take missingness into account. No interim analyses other than monitoring of demographic data are planned.

Continuous variables will be summarized according to intervention groups at baseline, if applicable, and end of trial using arithmetic or geometric means, standard deviations, ranges, and interquartile ranges as appropriate. Change from baseline will be summarized descriptively accompanied by its 95% CI. In descriptive summaries, last observation carried forward (LOCF) will be employed to impute missing values. Categorical variables at baseline and end of trial (if applicable) will be summarized as absolute number and proportion of subjects (%) according to intervention groups.

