#### Primary outcome

The primary study outcome is systolic BP assessed by 24 h ambulatory BP monitoring measured before and after three months of intervention. Systolic BP was chosen as the primary outcome due to its linear rise in relation to age and powerful prediction of cardiovascular events in older adults [15, 16]. The study timeframe was chosen to allow an adequate time range to effects (if any) take place, while optimizing trial logistics and participants adherence to interventions [7].

The ambulatory BP values will be treated as individual values for diurnal (from device placement to 10 PM, within the evaluation day), nocturnal (from reported sleep time to reported waking time) and 24 h periods, aggregated as group means at baseline and 12 weeks (trial end). Baseline measurements are carried out no longer than 30 days before the first intervention session whereas post-intervention assessment occurs within 10 days after the last session.

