### Sample size

Sample size for the primary outcome was calculated using estimates of effect sizes from (i) a meta-analysis of exercise training interventions and (ii) an randomized clinical trial based on a behavioral intervention for middle-aged patients with hypertension, evaluated by ambulatory BP monitoring, and analyzed in an intention-to-treat approach [7, 28]. We estimated that 184 participants would provide power values of 0.79 and 0.92 to detect differences of 2.5 mmHg and 3.0 mmHg between the two group mean values for the 24-h systolic BP, with an expected standard deviation of 6.0 mmHg. Such power calculation comprises: (1) an excess of 22 subjects due to the expected dropout rate (10–15%), (2) intraclass correlation of 0.1 in order to account the proportion that the center-to-center variance may affect the response variance, and (3) a two-sided significance level of 0.050 obtained from a mixed effects model fit without the treatment-by-center interaction.

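### The primary analysis may switch to independence GEE on an undefined look at the outcome data, and that method does not cure the problem that triggers it

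*Protocol article*

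**What the plan says.** In the Protocol article, Primary outcome, the endpoint has one value before and one after treatment: "The primary study outcome is systolic BP assessed by 24 h ambulatory BP monitoring measured before and after three months of intervention". Statistical considerations names the analysis: "Mixed effects models will be used to determine differences between groups using final values for systolic and diastolic ambulatory BP, adjusted for baseline values". The next sentence makes that choice conditional: "If these data present low linear fit, we will compare groups using generalized estimating equations with an independence model as the covariance matrix".

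The article gives no statistic, cut-off, time point or decision-maker for judging the fit. For the GEE it names no link, transformation, alternative mean model or cluster unit. The fallback sentence also does not repeat the baseline adjustment.

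Under Sample size, the two-sided 0.050 level is described as "obtained from a mixed effects model fit without the treatment-by-center interaction". The level and the power are therefore tied to the mixed model alone. Assignment of interventions and blinding states that data analysts are masked. The Discussion calls the trial confirmatory.

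**The concern.** A confirmatory trial needs one primary test, known before the outcome data are seen. Here two tests are possible, and which one applies depends on how the final BP values look, by a standard nobody has written down. Two analysts could both follow the text and report different primary P values.

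The remedy also misses its target. Poor linear fit is a problem of the mean model. GEE relaxes assumptions about variance and correlation and leaves the mean as specified. The switch therefore adds a choice without solving the problem that prompts it, and on one open reading it moves to a less precise estimator.

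**Working it through.** **1. The plan's own power figures.** The inputs, all from Sample size, are "We estimated that 184 participants would provide power values of 0.79 and 0.92 to detect differences of 2.5 mmHg and 3.0 mmHg", "with an expected standard deviation of 6.0 mmHg", "an excess of 22 subjects due to the expected dropout rate (10–15"%), and "intraclass correlation of 0.1 in order to account the proportion that the center-to-center variance may affect the response variance".

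- Evaluable: 184 − 22 = 162, or 81 per arm.
- SD after removing centre variance: 6.0 × √(1 − 0.1) = 5.692.
- Standard error: 5.692 × √(2/81) = 0.894.
- Non-centrality: 2.5/0.894 = 2.80 and 3.0/0.894 = 3.35.
- Power (non-central t, 160 df, two-sided 0.05): 0.793 and 0.915, which round to the stated 0.79 and 0.92.

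The figures reproduce for a model that takes centre variance out of the error. Nothing below changes them.

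**2. What the fallback does to the fit.** With identity link and independence working covariance, the GEE estimating equation is X′(y − Xβ) = 0, which is the least-squares equation. The fitted mean and the treatment estimate are therefore those of ordinary regression. In two sets of 2,000 simulated trials, one with a linear and one with a quadratic baseline relation, the largest difference between the two treatment estimates was below 1e-13. Only the standard error differs.

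**3. Reading A: final values, participant as unit.** Null simulations used 162 participants in two centres. The assumed values were residual SD 5, baseline slope 3 per SD and centre SD 6 × √0.1. Centre-adjusted ANCOVA stood in for the mixed model. In 4,000 trials, type I error was:

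| Test | Type I error |
|---|---|
| ANCOVA with centre | 0.052 |
| GEE, participant as cluster, no centre term | 0.045 |
| Significant under either | 0.053 |

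A further check found a correlation of about 0.996–0.998 between the two tests and an either-test error of 5.1–5.7%. The switch is nearly neutral here and achieves nothing for linearity.

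**4. Reading B: baseline and final values as repeated measures.** With arm, time and arm × time in the mean, independence GEE reproduces the difference in mean change. Let ρ be the baseline–final correlation, with equal variances σ² at both times. The article does not give ρ, so 0.6–0.8 is assumed.

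- Per-participant variance: 2σ²(1 − ρ) for change, σ²(1 − ρ²) for the baseline-adjusted final value.
- Ratio: 2/(1 + ρ), which is 2/1.6 = 1.25 at ρ = 0.6 and 2/1.8 = 1.11 at ρ = 0.8.
- Correlation of the two estimators: √((1 + ρ)/2), which is 0.89 and 0.95.
- Probability that at least one test is significant under the null: 7.1% and 6.5% in the large-sample normal calculation.

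Simulation with 162 participants agrees: about 12–22% more variance and 6.4–7.5% either-test error.

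**5. Clustering on centre.** With two centres the sandwich variance is built from two terms and is invalid. Simulated type I error was 0.39–0.41. The article does not state this reading. The figure shows only why any GEE must name its cluster unit.

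**The case against.** **Masking.** Analysts are masked, and judging linear fit does not require knowing the arms. This makes selection by result less likely, and that part stands. Masking does not supply the missing rule or repair the mismatch between trigger and remedy.

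**Non-linearity does little harm.** In a 1:1 randomised comparison, a misspecified linear baseline term mainly costs precision. That is correct, and it is also a reason not to switch the primary test.

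**The phrase may mean badly behaved residuals.** Robust standard errors would then be a partial remedy. That is plausible, but the text does not say it.

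**Details belong in the analysis plan.** Covariates and cluster unit often do, and a separate plan may define the trigger. The protocol itself, however, commits to a conditional change of primary method whose remedy does not fit its condition, which is more than an omitted detail.

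**Stronger readings.** Three inferences are tempting and not supported.

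- A reader might conclude that the fallback carries a 40% false-positive rate. That needs centre as the cluster, which Statistical considerations never says. A GEE working covariance conventionally describes correlation within a participant.
- A reader might assign a 5.9–7.1% error by assuming the two tests correlate 0.90–0.98. On final values with participants as units they correlate almost perfectly, and the inflation is negligible. An error of that order arises only under the repeated-measures reading, and only if the result guides the choice.
- A reader might say the fallback abandons the centre structure. This infers too much from silence, since the sentence on the mixed model does not mention centre either.

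**Conclusion.** The point holds in limited form. The primary method depends on an undefined criterion applied to outcome data, and the fallback leaves the fitted mean unchanged. Of the two readings with participants as units, one is nearly neutral (either-test error 5.1–5.7%). The other is worse: about 12–22% more variance and 6.4–7.5% either-test error, for an assumed baseline–final correlation of 0.6–0.8. The either-test figures are upper bounds that suppose the more favourable result is reported, which masking makes less likely. The switch can be neutral or harmful, and it offers no gain against poor linear fit. The stated power is unaffected. The severity is should-fix.

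**What to change.** Delete the conditional sentence in Statistical considerations. State that the primary analysis, whatever the fit, is the declared mixed model for 12-week 24-h systolic BP, adjusted for baseline 24-h systolic BP and accounting for centre as in the power calculation.

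Report the following only as named sensitivity analyses:

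- participant-level robust standard errors, or equivalently GEE clustered on participant with baseline and centre as covariates;
- a non-linear baseline term, such as a restricted cubic spline for baseline systolic BP.

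The robust regression should not replace the mixed model as primary, because it is in effect the fallback with a centre term added. If a separate analysis plan exists, it should carry the same wording, settled before unmasking. The cost is a short text change, with no extra data and no change to sample size or power.

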### Outcomes

In each center, both randomized groups are assessed for the outcomes listed below by standardized methodological procedures and a similar schedule (Table 3). Outcomes are measured for all randomized participants, irrespective of attendance or completion status. For participants who drop out of the study at any time after the randomization, research personnel use contact information to invite such individuals to undergo the end-study outcome assessments (12 weeks after intervention onset).

**Table 3 Tab3:** Time scheme for study conduction

	Study period							
	Enrolment	Baseline measures	Allocation and run-in^*^	Post-allocation			Close out	
TIMEPOINT**➔**	t-1	t0	t1	t2	t3	t4^†^	t5^†^	t5^†^
*Timepoint description*	Interviews	Occurs in 2 or 3 evaluation visits	–	Intervention Start	Evaluation visit (6th week)	Intervention end	Final evaluation visit 1	Final evaluation visit 2
ENROLMENT:								
Eligibility screening	x							
Informed consent	x							
Allocation			x					
INTERVENTIONS								
Combined exercise program				x	x	x		
Health education program				x	x	x		
ASSESSMENTS								
*Primary outcome*								
Ambulatory blood pressure		x					x	
*Main secondary outcomes*								
Office blood pressure		x					x	
Endothelial function^‡^		x			x		x	
Cardiorespiratory fitness^§^		x						x
*Other outcomes*								x
6-min walking test distance		x						x
SPPB		x						x
Quality of life questionnaires		x					x	
Autonomic function^‡^		x					x	
*Additional measurements*								
Anthropometric measurements		x					x	
Medication adherence scale (MMAS-8 Questionnaires)		x					x	
Blood variables collection		x					x	
Self-reported physical activity		x			x		x	
Grip strength		x			x			x

*SPPB* Short physical performance battery; *MMAS* Morisky Medication Adherence Scale. * = run-in period will be no longer than 2 weeks. † = time between t4 and t5 will be no longer than 2 weeks. ‡ = analysis of blood pressure and heart rate variability, exclusive for data collected at the coordinator center; § = cardiorespiratory fitness assessment occurs in a third separate visit at the participating center. Use of the©MMAS is protected by US copyright and registered trademark laws. Permission for use is required. A license agreement is available from [name], [name]; [contact]

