### Adherence assessments

Measures of adherence to interventions will be reported as group averages and operationalized as attendance and compliance. Attendance is monitored through session’s frequency recording and will be treated as the percent of intervention sessions experienced by a participant given the total number of scheduled sessions (36 sessions for the exercise program or 12 sessions for the education program). Adherence will be treated as the percent of intervention sessions fully accomplished without protocol deviations given the total number of scheduled sessions. For example, this may include either: (i) a participant allocated to the exercise program that, for any reason, walked less than the prescribed duration for a given session; or (ii) a participant allocated to the education program that only partially watched a lecture.

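### The per-protocol rule conflicts with itself twice: an unconditional sentence keeps dropouts whom the session minimum excludes, and the printed session counts fall below the stated 70%

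*Protocol article*

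**What the plan says.** All statements are in the protocol article.

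- **Set definition (Statistical considerations).** There are two analysis sets: a full analysis set of all randomized participants, and a PP set "including all subjects that completed the trial (completers) with adherence to at least 70% of the intervention sessions". The bracket that follows sets the minimum at "25 sessions for participants allocated in the exercise program" and "eight sessions for participants allocated to the education program", each as a greater-than-or-equal limit.
- **Dropouts (same section, next sentence).** "Participants that drop out of the study due to safety concerns or other outcomes will not be censored in PP analysis".
- **Completion (same section, missing-data paragraph).** It refers to "non-completers (defined as randomized subjects without 12-week data".
- **Follow-up after stopping (Outcomes).** "Outcomes are measured for all randomized participants, irrespective of attendance or completion status". For those who drop out, "research personnel use contact information to invite such individuals to undergo the end-study outcome assessments".
- **Counting sessions (Adherence assessments).** The programs schedule 36 exercise and 12 education sessions. "Adherence will be treated as the percent of intervention sessions fully accomplished without protocol deviations given the total number of scheduled sessions". Attendance is defined separately there as sessions experienced.

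**The concern.** The set definition and the sentence after it do not fit together. The first makes PP membership depend on completion and a session minimum. The second concerns people who stopped early, carries no condition about sessions, and uses the term *censored*, which has no defined meaning for a blood pressure taken at a fixed 12-week visit. Read plainly, not censored means not removed. The class it covers is also open-ended, since it extends beyond safety to other outcomes.

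The case in which the two sentences disagree is one the protocol foresees. The section on criteria for discontinuing allocated interventions lists cardiovascular events, hospitalization and severe health events as grounds for stopping in either arm, and the Outcomes section then tries to obtain 12-week data from those people.

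The minimum is also given in two forms, a percentage and a count, that do not agree.

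At stake is who belongs to one of the two analysis sets the plan names. The people in dispute under the first conflict are selected by clinical reasons for stopping, not at random. Muscle or joint injury is an additional stopping ground in the exercise arm only, so the disputed cases need not fall equally on the two arms.

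**Working it through.** **Inputs.** 36 and 12 scheduled sessions (Adherence assessments); 3 exercise sessions and 1 education session per week for 12 weeks (Interventions); 70%, 25 and eight (Statistical considerations).

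**1. The plan's own counts.**

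- Exercise: 0.70 × 36 = 25.2
- Education: 0.70 × 12 = 8.4

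Rounding to the nearest whole session gives 25 and 8, the printed counts. But a minimum of at least 70% has to be rounded up:

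| Arm | Printed count | As % of scheduled | Smallest count that is at least 70% | As % |
|---|---|---|---|---|
| Exercise | 25 | 25/36 = 69.4% | 26 | 26/36 = 72.2% |
| Education | 8 | 8/12 = 66.7% | 9 | 9/12 = 75.0% |

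The mismatch concerns only participants with exactly 25 exercise or exactly 8 education sessions.

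**2. The dropout sentence applied to each type of participant.** Completer is taken here as someone with 12-week data, the counterpart of the non-completer definition in the missing-data paragraph.

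| Participant | Set definition | Dropout sentence, plain reading | Dropout sentence, narrower reading |
|---|---|---|---|
| Stopped below the session minimum, has 12-week data | Out | In | Out |
| Stopped at or above the minimum, has 12-week data | In | In | In |
| Stopped, no 12-week data | Out (non-completer) | No final value to analyse | Out |

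The planned model compares final values adjusted for baseline. The two readings can therefore give different PP estimates only through the first row. Example: stopped for safety after 12 of 36 exercise sessions (12/36 = 33.3%) and measured at 12 weeks.

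**3. When a participant falls in that row.** Assuming the weekly schedule with no make-up sessions:

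- Exercise, stopped by the end of week 8: at most 3 × 8 = 24 sessions, below both 25 and 26.
- Education, stopped by the end of week 7: at most 1 × 7 = 7 sessions, below both 8 and 9.

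Anyone stopped for safety in the first 8 (exercise) or 7 (education) of the 12 weeks who returns for the final assessment is thus in dispute, whichever version of the count is used. This shows when the conflict can arise, not how often it will.

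**The case against.** The best defence is that the plain reading largely defeats the rule it follows. If an open-ended class of dropouts entered the PP set whatever their session count, the minimum would lose much of its purpose. The reading that lets both sentences work is that the reason for stopping is not itself a ground for removal; on it, the 12-of-36 participant is simply out. This reading is sensible and probably intended, but the text does not state it. So a reader might infer that the protocol supports two equally good PP sets, and that goes too far: one sentence is badly worded and a harmonising reading exists.

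Three other inferences are tempting and should not be drawn.

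- *That completer is undefined.* The missing-data paragraph largely settles it as having 12-week data. The mention of completion status in the Outcomes section is an instruction on data collection, not a definition of an analysis set.
- *That the session minimum is unusable.* An analyst given explicit whole numbers would ordinarily apply them. What stands is that they contradict the percentage beside them.
- *That membership would be chosen after seeing the data.* Only a journal article is at hand; a statistical analysis plan may fix the rule in advance, and the protocol states that data analysts are blinded. The article cannot show when the choice is made.

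The possible existence of an analysis plan does not remove the point, because the complaint is not missing detail. The published sentences and figures disagree with each other, and any later document would have to depart from one of them.

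**Conclusion.** The point holds as two internal conflicts in the stated PP rule: an unconditional dropout sentence set against a session minimum, and counts of 25 and 8 set against a percentage that requires 26 and 9. The second is plain arithmetic. The first depends on taking the dropout sentence at its ordinary meaning and on some early-stopped participants accepting the invitation to the 12-week assessment.

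Severity is minor. Primary and secondary outcomes are analysed by intention to treat on all randomized participants, and that analysis, the power and the sample size do not change. The document gives no basis for the number of participants affected or for the size or direction of any shift in the PP estimate. In particular, the injury criterion confined to the exercise arm does not establish a bias in either direction.

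**What to change.** In Statistical considerations:

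1. Replace the dropout sentence with: *Stopping for safety or another reason in itself neither admits nor excludes a participant; the session minimum applies to all.*
2. Define a completer consistently with the missing-data paragraph, as a participant with 12-week data for the outcome being analysed. A valid ambulatory recording should not be required for every PP analysis: that would needlessly drop people with, for example, a 12-week VO2peak but no valid ambulatory recording from PP analyses of other outcomes.
3. Make the threshold consistent: 26 and 9 sessions if at least 70% is meant, or keep 25 and 8 and remove the percentage.
4. State that sessions are counted by the adherence definition in Adherence assessments (completed in full, with no deviation), not by attendance.

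The cost is a few sentences of text. Visits, sample size and the intention-to-treat analysis stay as they are.

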#### Inclusion criteria

Diagnosis of hypertension as assessed by a previous ambulatory BP monitoring (no later than six months) or current use of anti-hypertensive drugs.Age ≥ 60 years old.Unchanged pharmacological scheme for four weeks prior enrollment.Willingness to participate in either intervention group.

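### The subgroup analysis of controlled versus non-controlled BP is defined by sample tertiles of baseline systolic BP, which rank participants but do not measure BP control

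*Protocol article*

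**What the plan says.** All the relevant text is in the protocol article.

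- **Statistical considerations, the question.** The subgroup analysis contrasts "individuals with non-controlled BP before the intervention versus individuals with well-controlled BP before the intervention".
- **Statistical considerations, the definition.** The next sentence fixes how the groups are formed: "Such stratification will be based on tertiles of systolic BP at baseline, with a primary interest in the comparison of interventions on ambulatory BP". That interest is placed in the two outer thirds. The sentence gives no mmHg value for control and does not say whether the systolic BP is office or ambulatory; Table 3 has both measured at baseline.
- **Statistical considerations, missing data.** The only term pairing BP status with group is in the list of variables for the pattern mixture model ("e.g., group, time, group by time, BP status, BP status by group"). It serves the missing-data sensitivity analysis, not the subgroup question.
- **Inclusion criteria.** Entry requires "Diagnosis of hypertension as assessed by a previous ambulatory BP monitoring (no later than six months) or current use of anti-hypertensive drugs". People whose BP is controlled on drugs can therefore enrol, and nothing fixes their share.
- **Sample size.** 184 participants, 22 of them for dropout; SD 6.0 mmHg; intraclass correlation 0.1; two-sided 0.05; power 0.79 at 2.5 mmHg and 0.92 at 3.0 mmHg. No subgroup power is claimed.

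**The concern.** BP control is a threshold idea: a person is above or below a stated pressure. A sample tertile is a relative position that moves with recruitment. The definition therefore does not deliver the groups that the label promises, and the middle third belongs to neither.

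The plan also does not say how a difference between subgroups would be judged. Whether the effect of exercise depends on baseline BP is a question about an interaction. If it were answered by looking at each outer third on its own, small strata would often give one significant and one non-significant result by chance. A statement that exercise works in uncontrolled but not in controlled hypertension could then rest on cut-points set by who happened to enrol, in a trial that its Discussion calls confirmatory.

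**Working it through.** **1. The plan's own power figures.** Evaluable participants: 184 − 22 = 162, or 81 per arm. Taking the intraclass correlation as removing centre variance, SD = 6.0 × √(1 − 0.1) = 5.69. A two-sample t-test then gives power 0.793 at 2.5 mmHg and 0.915 at 3.0 mmHg, which agrees with the stated 0.79 and 0.92. The SDs used below are 6.0 and 5.69.

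**2. Do the labels fit?** Let p be the share truly uncontrolled, defined by one cut-off on the same systolic BP that forms the thirds. The document does not give p, so these values are assumptions.

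| p | Result |
|---|---|
| 20% | All uncontrolled people are in the top third, so (1/3 − 0.20)/(1/3) = 40% of that third is controlled |
| 1/3 to 2/3 | Both outer thirds are labelled correctly; the middle third is mixed (all one kind only at the two ends) |
| 80% | All controlled people are in the bottom third, so (1/3 − 0.20)/(1/3) = 40% of that third is uncontrolled |

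**3. If the arms were compared separately within each outer third.** The expected number per arm per third is 162/6 = 27 after dropout, or 184/6 = 30.7 with everyone. SE = SD × √(2/n); t-test power, two-sided 0.05:

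| n per arm | SD | 95% CI half-width (1.96 × SE) | Power, 2.5 mmHg | Power, 3.0 mmHg |
|---|---|---|---|---|
| 27 | 6.0 | 3.20 | 0.324 | 0.438 |
| 27 | 5.69 | 3.04 | 0.354 | 0.476 |
| 30.7 | 6.0 | 3.00 | 0.362 | 0.487 |
| 30.7 | 5.69 | 2.85 | 0.394 | 0.528 |

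If the true effect is the same in both thirds, the chance that exactly one is significant is 2 × power × (1 − power). At 2.5 mmHg this is 2 × 0.324 × 0.676 = 0.44 up to 2 × 0.394 × 0.606 = 0.48. At 3.0 mmHg it is 0.49 to 0.50.

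**4. Information lost by using thirds.** Assume a normal baseline and a linear interaction. The outer thirds have mean ±1.091 SD, so a contrast of their labels keeps (2/3) × 1.091² = 0.793 of the information in the continuous baseline. Scoring all three thirds −1, 0, +1 keeps the same 79%. Leaving out the middle third but keeping the actual values keeps 1 − (1/3 − 2 × 0.431 × 0.364) = 0.98. The loss therefore comes from categorising, and hardly at all from setting the middle third aside.

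**5. What an interaction test could detect** (SD 6.0, 80% power, multiplier 1.96 + 0.84 = 2.80).
- Highest versus lowest third: SE = 6.0 × √(4/n) = 2.17 (184 participants) to 2.31 (162). Detectable difference in effects: 6.1 to 6.5 mmHg.
- Continuous baseline, all participants: SE per baseline SD = 2 × 6.0/√N = 0.885 to 0.943. Over the distance between the outer-third means (2 × 1.091 = 2.18 SD) the SE is 1.93 to 2.06. Detectable difference: 5.4 to 5.8 mmHg.

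**The case against.** A reader might infer that the middle third is thrown away. The text does not say so: it gives the outer thirds the primary interest and excludes nobody. As step 4 shows, setting the middle third aside would in any case cost only about 2% of the information if the actual values were kept.

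A reader might also infer that the plan requires separate tests in each third. The sentence is compatible with that reading, but equally with a joint model and an arm-by-third contrast. The choice of test is commonly left to the statistical analysis plan, which is not shown, so the absence of a named interaction test is not itself an error. Step 3 describes what would happen under one reading.

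Nor can it be said that the analysis is unable to show anything about BP control. The outer thirds do address dependence on baseline systolic BP, and if one third to two thirds of participants are uncontrolled, both outer labels are correct.

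Finally, the protocol claims no subgroup power, the analysis is an addition to the primary one, and the better method is weak too.

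All of this stands. It does not remove the mismatch between label and definition. That mismatch is in two consecutive sentences of the published text, and an analysis plan that followed them would inherit it.

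**Conclusion.** The concern holds as a mismatch of definition: sample tertiles of baseline systolic BP do not define controlled and non-controlled BP. The outer labels are fully correct only if the uncontrolled share happens to lie between about 1/3 and 2/3. At assumed shares of 20% or 80%, about 40% of one outer third would carry the wrong label. These figures assume a single systolic cut-off on the variable that forms the thirds.

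Two consequences are conditional. If the arms were tested separately within the outer thirds, power for 2.5 mmHg would be about 32-39%, and results would disagree about 44-50% of the time with an identical effect of 2.5-3.0 mmHg. If inference used tertile labels, about 79% of the information on a linear interaction would remain, assuming a normal baseline.

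The point is worth correcting, but it concerns a secondary analysis. The primary analysis and the sample size are untouched.

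**What to change.** - Base the subgroup inference on one arm by continuous baseline 24-h systolic BP interaction, added to the primary model and fitted to all participants. Report the coefficient with its 95% CI and the estimated effects at chosen baseline values, and label the analysis exploratory.
- Either call the strata thirds of baseline systolic BP and drop the control labels, or keep a controlled/non-controlled contrast defined by a fixed threshold. In the second case, state whether it applies to office or ambulatory BP, name it before unblinding, and judge it by the interaction term rather than by separate p-values.

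The cost is a change of wording and one extra model; no new data are needed. The model assumes that the effect changes linearly with baseline, which a spline can check. Power stays limited: 80% only for a difference in effects of about 5.4-5.8 mmHg between the outer thirds, so a null interaction should not be read as evidence of a uniform effect.
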